### Subjects

All patients participating in the HD-PPP programme between 1 March 2010 and 30 June 2014 will be included in the evaluation on process of care. All HD-PPP participants and an equal number of non-HD-PPP participants (eligible for HD-PPP but not participating) matched by age and gender will be included in the evaluation on the outcomes of care. The non-HD-PPP subjects will be selected from the HA patient database by the HA Statistics and Workforce Planning Department. Subjects will be recruited via a letter from the HA or on-site by HKU research assistants upon enrolment in the HD-PPP programme.

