#### Evaluation on outcomes of care

Anonymized data on clinical parameters at baseline, 12, 24, 36, 48 and 60 months after enrollment will be retrieved from the CMS by the HA statistics team.

For patient-reported outcomes, HD-PPP subjects and non-HD-PPP subjects will be invited in person at the community centre/renal unit to complete a telephone/face-to-face survey on health-related quality of life at enrolment into the HD-PPP (or equivalent time for non-HD-PPP), and then again at 12, 24, 36, 48 and 60 months. The follow up surveys will also include questions assessing patient enablement and global rating of change in health condition. The trained research assistant administering the patient-reported outcomes questionnaire survey will also obtain written informed consent from each patient prior to commencing the survey.

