### Three evaluation and feedback cycles

Three evaluation (audit) cycles will be conducted with each having a specific focus. The first evaluation cycle tries to identify discrepancies between intended targets and actual practice in which may require changes in the structure and process of care. The second evaluation cycle is to determine the standards that are achievable after the HD-PPP programme has been established. The third evaluation cycle aims to assess the sustainability of the standards of care, and to document the impact of the HD-PPP programme. Each evaluation cycle involves an initial planning meeting to agree on the criteria for evaluation and the target standards, site visits by the research team to observe the programme in action, to cross-validate structural and process elements and to clarify areas of confusion, the collection and analysis of preliminary data, and a feedback meeting with programme coordinators and administrators to discuss findings, identify areas for quality enhancement and revise the evaluation framework as necessary. The evidence generated by the study serves as an impetus for changes to be made to the programme.

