### Data analysis

Descriptive statistics on standard of care will be calculated including the percentage of centres meeting each structure criterion, percentage of subjects enrolled, dropped out, receiving criterion process including HD, and percentage of subjects achieving each outcome criterion.The difference in clinical and PRO of patients who take part in the HD-PPP programme at baseline, 12, 24, 36 and 48 months will be compared by paired sample t-tests.Independent sample t-test or chi-square test as appropriate will be used to compare the clinical outcomes between HD-PPP participants and control patients.Independent sample t-test or chi square test as appropriate will be used to compare the clinical outcomes between results achieved in different evaluation cycles.

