### Trial status

The first two evaluation cycles have been completed resulting in a final QOC evaluation framework developed for use in the third evaluation cycle based on new and revised indicators and target standards. The third evaluation cycle began in April 2012 and data collection is ongoing.

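### Evaluation cycles drawn from one repeatedly measured open cohort are compared with independent-sample tests, which are too conservative if patients recur and which mix cycle with time since enrolment

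*Protocol article*

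**What the plan says.** The Data analysis section fixes the between-cycle test: an independent-sample t-test or "chi square test as appropriate will be used to compare the clinical outcomes between results achieved in different evaluation cycles". The same section plans that programme patients' clinical and patient-reported values at baseline and at 12 to 48 months "will be compared by paired sample t-tests".

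The Subjects section defines one population, "All patients participating in the HD-PPP programme between 1 March 2010 and 30 June 2014", for the process evaluation. Its next sentence brings all participants, with an equal number of matched non-participants, into the outcome evaluation. Under Evaluation on outcomes of care, the data retrieved are "Anonymized data on clinical parameters at baseline, 12, 24, 36, 48 and 60 months after enrollment".

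Trial status reports that two cycles are complete and that the third began in April 2012, with a framework "developed for use in the third evaluation cycle based on new and revised indicators and target standards". The section on the three cycles gives sustainability of standards as an aim of the third. The article does not say which patients or which of their measurements make up a cycle.

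**The concern.** An independent-sample test assumes that the two groups share no patients. Here the groups are time slices of one continuing cohort, and nothing limits the third cycle to new entrants. The plan treats the same patients' repeated values as linked when they are grouped by follow-up month and as unlinked when they are grouped by cycle.

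Two things are at stake. First, the standard error of the between-cycle difference would be wrong. Second, an unadjusted contrast cannot separate the effect of feedback from that of longer time in the programme. Between-cycle change is how an audit spiral shows that feedback helped and that standards held. A test that tends to miss real decline makes it easier to conclude that standards were sustained.

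**Working it through.** The article gives no sample size, power or alpha for this comparison, so there is no planned figure to reproduce.

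**Effect of overlap on the variance.** Let the cycles hold n1 and n2 patients, with m patients in both, one value per patient per cycle, common SD s and within-patient correlation r.

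- Variance assumed by the test: s²(1/n1 + 1/n2).
- True variance: s²(1/n1 + 1/n2) − 2mrs²/(n1n2).
- Ratio true/assumed: V = 1 − 2mr/(n1 + n2). Writing f = 2m/(n1 + n2) for the effective overlap, V = 1 − fr.
- True two-sided level of a nominal 0.05 test: 2[1 − Φ(1.96/√V)].

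The documents give neither f nor r, so both are assumed. Power is illustrated for an assumed 120 patients per cycle and a difference of 0.3 SD, with SE0 = √(2/120) = 0.129:

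- independent test: Φ[(0.3 − 1.96·SE0)/(SE0√V)]
- test using the true variance: Φ[0.3/(SE0√V) − 1.96]

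| f | r | V | true level | power, independent test | power, correct variance |
|---|---|---|---|---|---|
| 0 | any | 1 | 0.050 | 64% | 64% |
| 0.5 | 0.3 | 0.85 | 0.034 | 65.3% | 71.2% |
| 0.5 | 0.5 | 0.75 | 0.024 | 66.3% | 76.5% |
| 0.5 | 0.7 | 0.65 | 0.015 | 67.4% | 82.2% |
| 0.75 | 0.3 | 0.775 | 0.026 | 66.0% | 75.2% |
| 0.75 | 0.5 | 0.625 | 0.013 | 67.7% | 83.6% |
| 0.75 | 0.7 | 0.475 | 0.0045 | 70.1% | 92.1% |

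**Chi-square version.** This was simulated with 20,000 runs, an assumed 120 per cycle and 80% attainment. With a within-patient phi of about 0.29, the true level is 0.036 at f = 0.5 and 0.023 at f = 1. With phi of about 0.57, it is 0.022 and 0.004. The pattern is the same.

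**Unequal cycles.** Assume 120 patients in an earlier cycle, 240 in the third, 100 in both, and r = 0.6. Then V = 1 − 2(100)(0.6)/360 = 0.67. The true level is about 0.016, and a contrast with 80% power under a correct analysis has about 66%.

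**Time since enrolment.** The earliest enrolment is 1 March 2010, and April 2012 is about 25 months later. The first possible 36-month value falls on 1 March 2013. If a cycle uses the data that arise during it, every 36-, 48- and 60-month value belongs to the third cycle.

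**Changed definitions, illustration only.** Suppose Kt/V had mean 1.4 and SD 0.25 (assumed) in every cycle. The proportion above a cut-off of 1.1, 1.2 or 1.3 would be 88%, 79% or 66%. A redefined criterion can therefore create a trend by itself. No document says that the Kt/V cut-off was redefined.

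**The case against.** The strongest defence is that cycle membership is undefined rather than shown to overlap. The Discussion reports 120 patients ever enrolled by 31 March 2012 and a waiting list, and inclusion runs to 30 June 2014, so the third cycle may hold many new patients. Measurements are anchored to months after enrolment. If the cycles compared different enrolment cohorts at the same follow-up month, the samples would be independent and the time confounding would also disappear. The article describes no such restriction, so this narrows the point without removing it. It does rule out some extreme figures: with 120 earlier patients all retained and 240 in the third cycle (assumed), f is at most 240/360 = 0.67.

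Three stronger readings are tempting, and the documents do not support them.

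- A reader might infer that largely the same patients are measured in each cycle. Overlap is likely, but its extent is nowhere given.
- A reader might infer that the p-values are invalid in a way that produces false improvements. With positive correlation and one value per patient per cycle, they are too large, so ignoring the pairing does not create a false gain.
- A reader might infer, from "The second evaluation cycle is to determine the standards that are achievable" and the revised framework, that targets were lowered or not truly pre-set and that any attainment trend is meaningless. But each cycle opens with a meeting to agree criteria and targets, and Methods/Design aims at a higher level of care each time. The between-cycle test covers clinical outcomes only; structure and process attainment is descriptive. Mean Kt/V and haemoglobin do not depend on targets, and a changed target percentage leaves the observed percentage unchanged. The Hypotheses section gives one Kt/V definition for 12 to 48 months.

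What stands of the third reading is limited. A proportion whose criterion was redefined, or an indicator new in a later cycle, has no like-for-like earlier value. The article does not show which these are, because the framework is in an additional file.

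**Conclusion.** The point holds in limited form. The plan names an independent-sample test for groups that its own design does not make independent, and it leaves cycle confounded with time since enrolment. For assumed f of 0.5 to 0.75 and r of 0.3 to 0.7, the true level is about 0.034 to 0.0045 instead of 0.05. In the 120-per-cycle illustration, power is roughly 6 to 22 percentage points below what a correct analysis would give.

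The direction rests on positive correlation and one value per patient per cycle. If several yearly values from one patient were entered as separate observations within a cycle, these figures would not apply. The confounding could bias the contrast either way.

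This should be fixed but is not critical. None of the three stated hypotheses is a between-cycle comparison, and the primary measures are proportions. It bears mainly on the third cycle's sustainability aim.

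**What to change.** 1. State which patients, and which of their measurements, form each evaluation cycle.
2. Replace the independent-sample tests between cycles with a mixed model (continuous outcomes) or a GEE (proportions), clustered on patient, with cycle as a factor and adjusted for time since enrolment. This adjustment does not remove survivor selection, and the report should say so.
3. For any outcome criterion compared across cycles as a proportion, apply one fixed definition to all cycles. Report new or redefined criteria separately, without a between-cycle test.

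The cost is slightly more analysis work and the loss of a between-cycle test for some redefined criteria. The first two changes need no new data. Applying one definition to earlier cycles may take some record work, because the Discussion notes that Kt/V was held in free text or on paper, or in an optional field.

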### Ethics, consent and permissions

This study has received ethics approval from the Institutional Review Board of the University of Hong Kong Hospital Authority Hong Kong West (UW 10–366), Hong Kong East (HKEC-2010-096), Kowloon East and Kowloon Central (KC/KE-10-0208/ER-3), Kowloon West (KW/EX/10-150 (34–17), New Territories East (CRE-2011.051) and New Territories West clusters (NTWC/CREC911-11). Written informed consent was received from each patient prior to commencing the survey.

### Trial status

The first two evaluation cycles have been completed resulting in a final QOC evaluation framework developed for use in the third evaluation cycle based on new and revised indicators and target standards. The third evaluation cycle began in April 2012 and data collection is ongoing.

## Discussion

The HD-PPP is a novel programme which is increasing the availability of publically funded HD for needy ESRD patients. With 725 patients receiving HD in publically funded hospitals as of December 31, 2011 [18] and a cumulative total of 120 patients ever being enrolled in the HD-PPP as of March 31, 2012, the HD-PPP has already expanded the capacity for HD by roughly 17 %. There remains a waitlist for available vacancies supporting the popularity of this programme. This evaluation study will provide objective evidence to inform decisions about its continuation and further expansion and to encourage ongoing improvements.

Two similar programme evaluation studies on the Risk Assessment and Management Programme for diabetic [19] and for hypertensive patients [20] in primary care are currently underway in Hong Kong. These authors highlight a variety of issues encountered when doing action research including the importance of stakeholder collaboration and communication, regular feedback and planning meetings, data monitoring and protocol adherence, which are also applicable to our evaluation of the HD-PPP programme. Some of the specific observations, lessons learned and challenges encountered as we carry out the HD-PPP evaluation study are discussed below.

### Partnership approach

The HD-PPP programme itself emphasizes the centrality of partnership between colleagues and organizations in the public and private sectors in order to successfully implement the programme. The study to evaluate the quality of care provided by the HD-PPP is also reliant on partnership to achieve its goals. Our academic research team is comprised of primary care clinician-researchers and statisticians whose expertise is in evaluation, and the study requires close partnership with those with complementary expertise in the content, logistics, information systems and patient care aspects of HD and the programme. This includes the programme administrative team from the HA head office, renal specialist colleagues in medicine and nursing from the HD-PPP workgroup, frontline clinical staff and programme coordinators at each of the 15 hospital renal unit and 7 community HD centre study sites, and members of the HA information technology and statistical teams. The diversity of the group brings multiple valid perspectives – and vested interests – to the evaluation study. Researchers seek to assure a rigorous approach to the evaluation based on solid theoretical frameworks, programme administrators focus on outcomes and resources while frontline health care providers may have concerns about workload and practical issues. As such, it is vital to build trust and mutual understanding in order to make this partnership and evaluation study effective. This is achieved by (i) emphasizing our shared goal to enhance the quality of the programme, rather than to blame or to find fault, which sets the tone of the project as one that is cooperative rather than contentious, (ii) having regular planning meetings in which candid discussion to negotiate a balance between the ideal and the practical may take place without compromising the rigour of the study, (iii) having timely and regular feedback meetings to share interim findings and to discuss actions to address shortfalls or difficulties, (iv) keeping and circulating accurate meeting records endorsed by attendees to ensure that discussion points, conclusions and action plans are clear, and (v) assuring participating study sites that information collected from structure of care questionnaires and site visits will be anonymized and presented collectively to encourage respondents to be honest and candid, which can also improve the validity of the results and permit all sites to learn from variations in practice.

### Evaluation framework development

The evaluation framework forms the crux of the evaluation study and its development is necessarily a detailed-oriented and collaborative but time-intensive effort. The aspects of the programme to be evaluated are derived from a review of the relevant international and local literature and information about the programme provided by stakeholders. The content is translated into an evaluation framework with target standards agreed upon by the group. The chosen target standard for each criterion should be set so that it encourages quality improvement but must balance what is ideal and desirable with what is realistic and achievable in the given context. The language used to articulate the criteria in the evaluation framework also matters, as it needs to accurately and unambiguously reflect the intention of the criterion. What may seem clear to the research group may be interpreted differently by a questionnaire respondent. For example, we had a criterion in an initial version of the structure of care questionnaire stating that “there must be a record of enrolled patients kept in the electronic patient record” which inadvertently addresses two issues: whether there is a record of enrolled patients, and whether the electronic patient record is used to keep the enrolment record. A respondent may respond “no” if either part is not fulfilled which will make data interpretation difficult without further clarification. Though the structural template of the evaluation framework remains fixed, the specific content evolves because of the iterative nature of the evaluation process and the evolution of the HD-PPP programme itself over time.

### Value of direct observation

Site visits to all the study sites help to assure and cross-validate quality of structure and process of care, to observe the implementation of quality enhancement strategies, to note variations in practice, and to document good practices or improvements in practice to share across the programme. Direct observation of the programme in action across all the study sites enables us to see the written programme protocol operationalized. It is an opportunity to see the facilities and to gain an understanding of how electronic platforms are used and accessed, to get feedback from the front line healthcare staff about their true experience and to follow a patient journey from beginning to end. All of this contributes to our understanding of the programme including its constraints and possibilities, and strengthens the relationship with the colleagues at the study sites.

### Potential to realize change

Even before results are compiled, the process of evaluation is a valuable exercise. It draws attention to practices that are taken for granted and motivates change. For example, Kt/V is widely recognized as a good indicator of dialysis adequacy and is used in clinical practice for patient management. It is also the primary clinical outcome indicator for this evaluation study. In the process of collecting data, we noted that it was not easy to collect Kt/V data because it is recorded in the open-text clinical consultation notes section of the electronic patient record or manually in paper record summaries, which cannot be extracted automatically. For patients in the HD-PPP a separate module of the electronic patient record has a designated Kt/V field but completing it is optional. To optimize the usefulness of Kt/V data, these need to be recorded in such a way that is systematic and easily retrievable by those involved in the patient’s care. This was discussed during a feedback meeting with the HD-PPP workgroup, leading to a pragmatic solution ensuring that Kt/V of every dialysis patient would be recorded annually in the electronic renal patient registry.

## Conclusion

As the demand for HD grows, programmes such as the HD-PPP will help to shorten the waiting time for HD for ESRD patients and relieve the burden on public hospitals. A formal, independent and rigorous evaluation is necessary to assure that the programme is achieving its purpose and having a positive impact on patient care.

## Abbreviations

A&E, accident and emergency; CMS, computerized medical record system; ESRD, end stage renal disease; GRS, global rating scale; HD, haemodialysis; HD-PPP, haemodialysis public-private partnership; HKU, the University of Hong Kong; KDQOL, Kidney Disease Quality of Life; LDL-C, low density lipoprotein-cholesterol; PD, peritoneal dialysis; PEI, patient enablement instrument; PRO, patient reported outcome; QOC, quality of care; RRT, renal replacement therapy; SF-12v2, short form-12 version 2; SOPC, specialist outpatient clinic
